# Laparoscopic bridging vs. anatomic open reconstruction for midline abdominal hernia mesh repair [LABOR]: single-blinded, multicenter, randomized, controlled trial on long-term functional results

**DOI:** 10.1186/1745-6215-14-357

**Published:** 2013-10-28

**Keywords:** Incisional, Midline, Hernia, Laparoscopy, Mesh, Functional results, Rives, Randomized

## Abstract

**Background:**

Re-approximation of the rectal muscles along the midline is recommended by some groups as a rule for incisional and ventral hernia repairs. The introduction of laparoscopic repair has generated a debate because it is not aimed at restoring abdominal wall integrity but instead aims just to bridge the defect. Whether restoration of the abdominal integrity has a real impact on patient mobility is questionable, and the available literature provides no definitive answer. The present study aims to compare the functional results of laparoscopic bridging with those of re-approximation of the rectal muscle in the midline as a mesh repair for ventral and incisional abdominal defect through an “open” access. We hypothesized that, for the type of defect suitable for a laparoscopic bridging, the effect of an anatomical reconstruction is near negligible, thus not a fixed rule.

**Methods and design:**

The LABOR trial is a multicenter, prospective, two-arm, single-blinded, randomized trial. Patients of more than 60 years of age with a defect of less than 10 cm at its greatest diameter will be randomly submitted to open Rives or laparoscopic defect repair. All the participating patients will have a preoperative evaluation of their abdominal wall strength and mobility along with volumetry, respiratory function test, intraabdominal pressure and quality of life assessment.

The primary outcome will be the difference in abdominal wall strength as measured by a double leg-lowering test performed at 12 months postoperatively. The secondary outcomes will be the rate of recurrence and changes in baseline abdominal mobility, respiratory function tests, intraabdominal pressure, CT volumetry and quality of life at 6 and 12 months postoperatively.

**Discussion:**

The study will help to define the most suitable treatment for small-medium incisional and primary hernias in patients older than 60 years. Given a similar mid-term recurrence rate in both groups, if the trial shows no differences among treatments (acceptance of the null-hypothesis), then the choice of whether to submit a patient to one intervention will be made on the basis of cost and the surgeon’s experience.

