## Design

LABOR is a randomized, controlled, non-inferiority trial. Patients will be randomly allocated to receive a mesh repair of their incisional hernia with either laparoscopic bridging or open anatomical reconstruction. The trial has been registered on Current Controlled Trials as ISRCTN93729016.

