### Sample size calculation, randomization and statistical analysis

On the basis of a previous published work, the minimum DLL to define the non-inferiority of laparoscopic bridging vs. anatomic open reconstruction will be set to 5 degrees with a standard deviation of 8.5 degrees. With this hypothesis and for a power of 90% and an alpha of 5%, we will need 50 patients in each arm (total 100). If we consider a possible dropout rate of 10%, a total of 110 patients would be sufficient. As a consequence, approximately 20 patients for each center will be required.

A centralized block randomization stratified for center will be performed by a statistician not involved in patient management. Blocks will have a variable dimension (random) between 4 and 12 units. A total of five blocks will be obtained for each center in the event that the investigator continues enrollment beyond the initially planned sample size. The local investigators, after obtaining written informed consent of patients, will receive the randomization arm from the statistical center for each patient, then the patient will be allocated to the treatment group as indicated.

Data analysis will be performed by a statistician not involved in data collection at the main investigation center (University of Genoa). The means and standard deviations or medians with ranges, if asymmetry of data is detected, will be reported for all continuous demographic and clinical characteristics recorded, whereas counts and percentages will be recorded for categorical characteristics (e.g., gender, functional status and smoking habits).

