To compare the DLL test results during follow-up between the two groups of treatment, ANOVA for repeated measures will be adopted using DLL as the dependent variable. Because the DLL test cannot have a normal distribution, a ranking transformation will eventually be used. The same approach will be used for the other ordinal characteristics used as secondary outcomes (VAS as scoring for pain and AWS score) and, in general, for all other outcomes considered. If a consistent number of missing values is detected during the follow-up, ANOVA for repeated measures will be replaced by linear mixed or generalized estimating equation (GEE) models, which permit the exclusion of the data only from a single missing observation and not from the patient on overall as with ANOVA. Single comparisons between baseline values and each time during follow-up will be assessed using Bonferroni correction for multiple comparisons. All analyses will be performed on an intention-to-treat basis. A *p*-value lower than 0.05 will be considered statistically significant. SPSS (v.20, IBM Corp., Armonk, NY, USA) will be used for the statistical analyses.

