### Clinical implications

Given the constant and equal number of recurrences in both groups, if patients submitted to laparoscopic repair have the same results in physical testing in comparison with open repair, then the trial would indicate (*acceptance of the null hypothesis*) that an anatomic repair of incisional hernia through rectal muscles medialization does not offer any advantage to the patient. The reasons for this deduction could be twofold: first, the anatomic repair is not effective on previously scarred tissue, and, second, the dimensions of the defect included in this trial are too small to determine a perturbation of the abdominal motility. The clinical implications for these results would be that the laparoscopic bridging hernia repair in patients over 60 years of age should be considered a valid alternative to open repair, for both its efficiency and functional, or even superior, results given the advantages already demonstrated in previous trials (fewer wound complications, shorter postoperative hospital stay). It would remain an open question whether the restoration of the anatomic abdominal structure would be useful in younger patients. If the results reveal a better test performance in the anatomic reconstruction group (*rejection of a null hypothesis*), the choice of this type of intervention as the gold standard technique would be supported by clear evidence of an advantage offered in terms of the functional restoration of the abdominal wall.

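### The trial is designed and sized for non-inferiority with a 5-degree margin, but the stated analysis and conclusions treat failure to find a difference as proof for bridging

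*Protocol article*

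**What the plan says.** - **Design:** "LABOR is a randomized, controlled, non-inferiority trial".
- **Sample size calculation, randomization and statistical analysis**, first paragraph: "the minimum DLL to define the non-inferiority of laparoscopic bridging vs. anatomic open reconstruction will be set to 5 degrees". The SD is taken as 8.5 degrees. Power is 90% and alpha 5%, with no sidedness given, and the result is that "we will need 50 patients in each arm".
- **Same section, analysis paragraph:** DLL is compared between groups over follow-up by repeated-measures ANOVA, possibly after a rank transformation, or by mixed or GEE models if many values are missing. A p-value "lower than 0.05 will be considered statistically significant". The 5 degrees are not mentioned again.
- **Abstract, Discussion:** given similar recurrence, "if the trial shows no differences among treatments (acceptance of the null-hypothesis"), the choice of operation is left to cost and surgeon experience.
- **Clinical implications:** equal physical-test results are again labelled acceptance of the null, and are taken to show "that an anatomic repair of incisional hernia through rectal muscles medialization does not offer any advantage to the patient". A better result in the open arm is labelled rejection of the null and is said to support open reconstruction as the gold standard.

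**The concern.** In a non-inferiority trial the null hypothesis is that the new treatment is worse by at least the margin, and the new treatment is supported by rejecting that null. Here the null in the Abstract and in Clinical implications is no difference, and bridging is supported by failing to reject it. The two logics run in opposite directions.

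Two consequences follow. First, small numbers, missing data or a large SD make a non-significant result more likely, and so make the favourable conclusion for bridging easier to reach. The error that the sample size was built to limit, accepting bridging when it is 5 degrees worse, is not controlled. Second, a statistically significant deficit smaller than 5 degrees would be read as establishing open repair, although the trial's own limit treats a deficit of that size as tolerable.

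**Working it through.** **Inputs.** Margin 5 degrees, SD 8.5, power 90%, alpha 5%, 50 per arm (all from the sample size section). Assumed, because not stated: true difference 0 for sizing; SD 8.5 applies to the 12-month comparison; a two-sample t-test stands in for the ANOVA. A higher DLL angle of interest is better (scoring table in the DLL section), so the deficit is open minus laparoscopic.

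**1. Reproduce the sample size.**

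n per arm = 2 × [SD × (z₁₋α + z₁₋β) / margin]²

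- One-sided 5%: 2 × [8.5 × (1.645 + 1.282) / 5]² = 49.5, so **50**, as stated.
- One-sided 2.5%: 2 × [8.5 × (1.960 + 1.282) / 5]² = 60.7, so 61. This is also the number for a two-sided 5% difference test of 5 degrees.

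The stated 50 is therefore a one-sided 5% calculation and does not match the two-sided difference test.

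**2. Standard error.** SE = 8.5 × √(2/50) = 1.70 degrees, 98 degrees of freedom.

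**3. The two rules on the observed deficit.**

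- Difference test: non-significant if the observed deficit is below 1.984 × 1.70 = 3.37 degrees.
- Margin test at one-sided 5%: non-inferior if the observed deficit is below 5 − 1.661 × 1.70 = 2.18 degrees.
- Margin test at one-sided 2.5%: below 5 − 1.984 × 1.70 = 1.63 degrees.

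An observed deficit between about 2.2 and 3.4 degrees would be read as no difference although its one-sided 95% limit lies above 5 degrees. The correct reading is inconclusive, a category the article does not have.

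**4. How often bridging is accepted when it is truly 5 degrees worse** (noncentral t, 50 per arm):

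| SD | SE | P(non-significant) | Margin test, one-sided 5% |
|---|---|---|---|
| 8.5 (stated) | 1.70 | 17% | 5% |
| 10 (illustration) | 2.00 | 30% | 5% |
| 12 (illustration) | 2.40 | 46% | 5% |
| 15 (illustration) | 3.00 | 62% | 5% |

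With 45 analysed per arm and SD 8.5, the 17% becomes 21%. The margin test keeps its 5% whatever the SD or n. At SD 15 the smallest significant deficit is 1.984 × 3.00 = 5.95 degrees, so even an observed deficit larger than the margin could be read as no difference.

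**5. A true deficit inside the margin.** For a true 3-degree deficit at SD 8.5, the difference test is non-significant 58% of the time and significant 42% of the time.

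**6. Power once the margin is tested** (50 per arm, true difference 0, normal approximation). One-sided 5%: Φ(5/1.70 − 1.645) = 90.3%. One-sided 2.5%: Φ(5/1.70 − 1.960) = 83.7%.

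**The case against.** Four objections deserve an answer.

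- **The analysis plan is not shown and may compare a confidence limit with 5 degrees.** It may, and the models named can supply such an interval. The silence of the analysis paragraph would not be a finding by itself. But the article also states, twice and in the language of hypothesis testing, a conclusion rule that is wrong for the declared design. A margin test in the analysis plan would contradict that rule rather than complete it.
- **The Abstract and Clinical implications are interpretive prose, not a formal decision rule.** Neither gives a p-value, and reading non-significance as acceptance means joining them to the analysis paragraph. That reading is fair: acceptance and rejection are testing terms, and the only criterion given is p < 0.05.
- **The error rates are for a t-test that is not the planned analysis.** This is correct. The true rates depend on the within-patient correlation, on which ANOVA effect is tested and on whether ranks are used, none of which is given. Only the 17% rests on the document's own SD; SDs of 10, 12 and 15 are illustrations. The direction does not depend on these choices.
- **A significant 3-degree deficit is a real difference.** This also stands. Open repair can be superior while bridging is non-inferior. The fault is narrower: Clinical implications moves from any better result to a gold standard without reference to the 5-degree limit, although the article's own Discussion warns that a significant difference may be clinically irrelevant.

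**Conclusion.** The concern holds; the rule is wrong as written. The design and sample size are for non-inferiority with a 5-degree margin, and 50 per arm is reproduced exactly at one-sided 5%. The stated analysis is a difference test, and the stated conclusions take acceptance of no difference as support for bridging. Under that rule the chance of accepting bridging at a true 5-degree deficit is about 17% instead of 5%, assuming 50 analysed per arm, SD 8.5 and a two-sided t-test at 12 months. It grows with a larger SD or fewer analysed patients. The sample size itself is not at fault. Because this governs the primary conclusion, it must be corrected before the data are analysed.

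**What to change.** 1. State the null hypothesis: the mean difference (open minus laparoscopic) in DLL change from baseline to 12 months is 5 degrees or more. This uses the outcome as defined under Primary outcome.
2. Estimate that difference in degrees, for example from a baseline-adjusted or mixed model, with its confidence interval. Keep any rank-based analysis as a sensitivity analysis, because ranks cannot be compared with a margin in degrees.
3. Declare non-inferiority only if the upper confidence limit is below 5 degrees. Call an interval that crosses 5 degrees inconclusive. Test superiority of either arm only as a further step, and interpret any difference against the 5-degree limit.
4. State the level. One-sided 5% (upper limit of a two-sided 90% interval) matches the 50 per arm and keeps about 90% power.
5. Replace the acceptance and rejection wording in the Abstract and in Clinical implications with this rule.

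**Cost:** wording only, with no added patients or data, if one-sided 5% is fixed. If one-sided 2.5% is preferred, either accept 83.7% power at 50 per arm or plan 61 per arm: 122 in total, and 122 / 0.90 = 135.6, so 136 with 10% dropout.

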**Trial registration:**

Current Controlled Trials ISRCTN93729016

## Background

Incisional hernia is one of the most common complications following abdominal surgery, with a reported incidence of 3-13% [1,2]. It is evident from recent trials that mesh adoption for the repair of these abdominal wall defects has dramatically reduced the recurrence rate after surgery in comparison with traditional simple suture repair [3,4]. Nevertheless, the best technique for the repair of an incisional hernia to date has yet to be defined. In fact, a recent meta-analysis on the open repair of incisional hernias [5] was not able to demonstrate the superiority of any of the available repairs independently from the mesh placement in the abdominal wall (onlay, sublay and inlay), the type of mesh used (lightweight, heavyweight) or the addition of anatomical dissection aimed at increasing abdominal compliance (i.e., component separation).

These findings could support the following hypotheses:

•The good results, in terms of recurrence, obtained with each technique could have a key point in the adoption of a mesh.

•The superiority of one technique over another should be based on outcomes other than hernia recurrence.

Very little evidence [6,7] and recently a large prospective trial [8] comparing laparoscopic and open techniques in terms of a quality of life (QOL) measurement tool specific for hernia outcome study (the Carolina Comfort Scale) have indicated a possible benefit in the short term granted by the open fascial closure of the abdominal defect. Basing their assumption on these observations and on the equivocal results on QOL from trials comparing laparoscopic and open ventral hernia repair [9,10], experts in the field [11,12] have hypothesized that medialization of the rectus abdominis muscles improves abdominal wall function. This speculation has not been objectively proven because measures of the recurrence rate, quality-of-life scores and patient questionnaire responses remain the only established criteria for assessing abdominal wall function after hernia repair. Nevertheless, expert groups recommend this approach for ventral hernia repair as a rule to centralize and re-approximate the rectus muscles along the midline to the extent possible. This step attempts to restore the functional, innervated abdominal wall and perform dynamic reparation without undue tension. Commonly used techniques with the aforementioned characteristics that have been used for the repair of abdominal hernias include retrorectus (i.e., the Rives-Stoppa procedure) and component separation (the Ramirez technique). Thus, several surgeons consider these the current “gold standard” treatments.

Based on this assumption, even if laparoscopic surgery has gained an adequate scientific consensus for the surgical treatment of different diseases [13,14], certain criticisms have been raised over its introduction in the routine practice of abdominal hernia repair. These techniques, which avoid the restoration of anatomical integrity for a simple bridging of the defect, appear “less effective.”

Nevertheless, a recent systematic review of studies comparing laparoscopic and open techniques [15] was not able to confirm this assumption. On the contrary, the review indicated that laparoscopic incisional hernia repair is generally safe, with a lower risk of wound infection and shorter hospital stays relative to open surgery.

Surprisingly and in opposition to previous studies included in the Cochrane review, a recently published randomized trial [16] indicated that postoperative pain and recovery at 3 weeks is not affected by the type of adopted hernia repair, but the laparoscopic approach results in better physical function than the open repair based on SF36 subscale values. This observation is only partly the consequence of the reduced number of surgical site infections following laparoscopy. Moreover, these findings could support the hypothesis that procedures aimed at restoring the anatomy that involve extensive and potentially damaging dissection in an already scarred myoaponeurotic region could be less effective for the patient. In other words, in certain circumstances, anatomic reconstruction could be an excessive burden for an already compromised abdominal wall. Nevertheless, a self-reported questionnaire cannot be accepted as the sole explanation of this phenomenon, which should be objectively investigated and measured.

To obtain an answer to the debate, an emerging type of analysis is being more frequently used: the functional evaluation of the motility and muscular strength of the abdominal wall. The modalities to evaluate the trunk flexor muscles and the strength of the abdominal wall are isokinetic dynamometer measurement and physical testing.

The isokinetic dynamometer (Biodex Model 2000, Multijoint System 3, Biodex Corp., Shirley, NY, USA) is a safe way to load a dynamically contracting muscle to maximum capability throughout its entire range in a continuous motion and to evaluate the trunk flexor strength during isokinetic movement at a constant angular velocity. An inexpensive alternative to using a machine for evaluation is the use of physical tests. The most commonly used tests are the double leg-lowering test (DLL) and the trunk-raising test (TR). Both of them explore the strength of the rectal muscle, asking the patient to perform some curl-type exercises. After categorization of DLL and TR, it is possible to create an abdominal wall strength score (AWS) with a minimum score of 0 and a maximum of 10 points.

Thus far, the aforementioned instruments have been used in two published studies without resolving the debate over the best intervention between bridging and reconstruction of the abdominal wall. The dynamometer was used in a study by den Hartog and coworkers [17] in which trunk flexor strength was compared for a group of 30 patients submitted to laparoscopic or open hernia repair with rectal approximation and a group of 12 healthy subjects. The mean torque/weight (N m/kg) for trunk flexion was significantly higher in the control group compared with that of the incisional hernia repair patients. Moreover, among the patients who underwent surgery, a significantly higher peak torque/weight was observed in the open technique group compared with the laparoscopic technique group. Based on these measures, the authors considered the two-layered technique more effective in repairing the abdominal wall of patients with incisional hernias and even more protective against some types of complication (back pain) in comparison with laparoscopic bridging. The multiple limitations represented by the fact that the study was not prospective and largely underpowered and that the patients in the open surgical group were submitted to a repair without mesh make the results not completely reliable.

The data for the physical testing method appear to be more interesting. The data available for the DLL and TR tests and combined AWS score are currently validated in clinical practice [18], but results for incisional hernia are still not available. The adoption of this type of test to evaluate the results of incisional and ventral hernia repair could be interesting because such results would aid in discerning whether, hypothetically, the advantage granted by anatomical reconstruction over laparoscopic bridging is real and the data provided by the dynamometer can be translated into clinical practice. The hypothesis of the study is that, for abdominal ventral defects suitable for a laparoscopic repair (10 cm at major dimension), the bridging technique is similar to the open reconstruction in terms of restoration of abdominal wall function. We believe that the best way to demonstrate this hypothesis is by measuring the differences among these groups in a clinical variable with a real impact for the patients (physical testing, i.e., DLL, TR, AWS score). The results of the physical testing will be correlated with clinical parameters (respiratory function tests, intraabdominal pressure, CT volumetry and quality of life) in order to better address the physiological implications of each of the repair techniques.

### Aim of the study

The aim of this study is to define the role of anatomical reconstruction and simple defect bridging in the mesh repair of incisional and primary ventral hernias. We wanted to analyze in depth whether defect bridging is comparable to anatomical reconstruction with mesh in terms of the strength of the abdominal wall as expressed by the differences among groups 1 year postoperatively in the grades of leg extension over the trunk during a DLL test.

